### Intervention condition

The intervention in use (GET.ON Mood Enhancer) 46 consists of six consecutive modules, each about 30 min in length, and homework assignments. Participants are recommended to work on one or two modules per week. Adaptations of the intervention have proven effective in reducing depressive symptoms in varying samples [46–51]. The intervention has been slightly modified to suit the purpose of this setting (wording of the introduction, example participants, explanation of further treatment options, and text message support).

The intervention is based on behavioral activation [52] and problem-solving therapy [53]. The core elements of the intervention are (1) psycho-education, (2) behavioral activation, (3) systematic problem solving, and (4) optional lections on sleep, rumination, and relaxation. Additionally, participants receive access to an electronic mood diary. Participants receive a semi-standardized feedback after each completed module by an e-coach (trained psychologist) in order to enhance adherence. Feedback includes positive reinforcement of the participants’ assignments and encouragement to continue working with the intervention. E-coaches are not otherwise involved in the study. Additionally, participants can chose to activate text message support (42 text messages, one per day). The text messages are standardized and remind the participants of their weekly assignments and repeat specific lessons. Text message prompts and guidance have been shown to be very beneficial for the efficacy and adherence to web-based interventions [33, 54, 55]. Participants also receive standardized e-mails reminding them of unfinished tasks. Participants can access the intervention at any time and from all web-enabled devices. Each module closes with a short questionnaire, assessing subjective usefulness of the module, the location and time spent working on the module, and the level of concentration.

Participants’ access to TAU (e.g., visits to other medical practitioners) is not restricted. A detailed description of TAU is obtained at post-treatment. Any contact between the research team and study participants (e.g., online assessments, e-mail reminders) is standardized for all study participants (IG and CG) and reduced to a minimum.

### Control condition

Participants of the waiting control group are informed that they can access the web-based intervention after follow-up assessments. Again, access to TAU until follow-up assessment is not restricted. As for the intervention group, a detailed description of TAU is obtained at post-treatment.

## Outcome measures

Table 1 gives an overview of assessments at screening, baseline, post-treatment and follow-up.

**Table 1 Tab1:** Overview of measurements

Variables	Instrument	Screening	T1	T2	T3
Inclusion/exclusion criteria					
Age	SR	x			
Internet access	SR	x			
Depressive symptoms	CES-D	x			
Non-Suicidality	BSI item 9		x		
Effectiveness					
Primary outcome					
Depressive symptoms	CES-D	x	x	x	x
Secondary outcomes					
Depressive symptoms (categorical)	PHQ-9		x	x	x
Health-related quality of life	SF-12		x	x	x
Psychological symptoms	BSI		x	x	x
Attitudes towards psychotherapy	ATSPPH-SF		x	x	x
Attitudes towards web-based interventions	ATSPPH-SF (adapted version)		x	x	x
Adverse events	INEP			x	
Acceptance					
Motivation to use a web-based intervention	SR	x			
Intervention adherence	Response and dropout rate	x		(x)	
Intervention satisfaction	CSQ-8			(x)	
Sample characteristics					
Demographic variables	SR		x		
Internet affinity	IAS		x		
Health care utilization	FIMA			x	
Current Psychotherapy	SR		x	x	x

Note. *T1* baseline, *T2* post-treatment, *T3* follow-up, *x* intervention and control group, *(x)* only intervention group, *SR* self-report, *CES-D* Center for Epidemiologic Studies Depression Scale, *BSI* Brief Symptom Inventory, *PHQ-9* Patient Health Questionnaire, *SF-12* Health Survey, *ATSPPH-SF* Attitude Towards Seeking Professional Psychological Help- Short Form, *INEP* Inventory for the Assessment of Negative Effects of Psychotherapy, *CSQ-8* Client Satisfaction Questionnaire, *IAS* Internet Affinity Scale, *FIMA* Questionnaire for Health-Related Resource Use in an Elderly Population

### Effectiveness measures

#### Primary outcome

##### Depressive symptoms

Depressive symptoms are assessed using the Center for Epidemiologic Studies Depression Scale (CES-D; German version [42]). The CES-D consists of 20 items measuring the global level of depressive severity within the last week on a 4-point Likert scale. The total score ranges from 0 to 60, with higher scores indicating more severe depressive symptoms. Its internal consistency of *α* = .92 in clinical samples is very good [42].

#### Secondary outcomes

##### Depressive symptoms

The Patient Health Questionnaire (PHQ-9; [56]) allows a categorical classification of depression severity, distinguishing between moderate, moderately severe and severe major depression. It consists of nine items and assesses depressive symptoms of the past two weeks. Its internal consistency reaches values of *α* = .88 [57].

##### Health related quality of life

To assess health related quality of life, the SF-12 Health Survey [58] is used. The instrument provides two subscales, measuring physical and mental quality of life components. It consists of 12 items, rated on scales between two and five points. Reliability and validity of the SF-12 have been well documented (*α* = .77; [58]).

##### Psychological symptoms

The Brief Symptom Inventory (BSI; [43]) is applied to measure psychological symptoms of the past week. Its 53 items are rated on a 5-point Likert scale and cover symptoms of somatization, obsessive compulsion, interpersonal sensitivity, depression, anxiety, hostility, phobic anxiety, paranoid ideation and psychoticism. The Global Severity Index (GSI) reflects the respondents’ overall level of psychological distress. Validity and reliability of the BSI are well-established (*α* = .91; [43]). Additionally, item number 9 of the BSI serves as an indicator for suicidal ideation.

##### Attitudes towards psychotherapy

Participants’ attitudes towards face-to-face psychotherapy are measured by the Attitude Towards Seeking Professional Psychological Help Scale - Short Form (ATSPPH-SF; [59]). This instrument consists of 10 items that are rated on a 4-point Likert scale. The psychometric properties of the questionnaire are good (*α* = .78; [60]).

##### Attitudes towards web-based interventions

An adapted version of the Attitude Towards Seeking Professional Psychological Help Scale - Short Form (ATSPPH-SF; [59]) is applied to assess the attitude towards web-based interventions. Compared to the original version of the ATSPPH-SF, solely the term “psychotherapy” is replaced by the term “online training” in each item. The number of items remains unchanged.

##### Adverse events

The Inventory for the Assessment of Negative Effects of Psychotherapy (INEP; [61]) consists of 21 items dealing with potential side effects of psychotherapy. In accordance with previous studies [62–65], the instrument is adapted for the particular setting of web-based interventions, resulting in the deletion of 6 face-to-face specific items. The remaining 15 items are scored on a 4-point Likert scale. The reliability of this instrument is good (*α* = .86; [61]).

#### Acceptance measures

##### Intervention adherence

The adherence to the intervention in use is depicted by the take-up rate at the level of recruitment and the number of modules completed. Additionally, the intervention dropout relates to the number of intervention completers (≥ 5 modules; [46]) and non-completers in the IG. For a better understanding of intervention dropouts, all non-completers are asked to indicate reasons for their non-completion.

##### Intervention satisfaction

The Client Satisfaction Questionnaire (CSQ-8; [66]) measures client satisfaction with health care services. Following Boss and colleagues [67], we use an adapted version for the evaluation of satisfaction with web-based interventions for IG-participants at post-treatment. The scale consists of eight items, rated on a 4-point Likert scale. The adapted scale has been validated, indicating high reliability and construct validity [67]. In addition to intervention satisfaction, one item assesses technical difficulties dealing with the intervention. This item will be evaluated separately.

##### Motivation to use a web-based intervention

In order to gain an understanding of how interested respondents differ from non-interested respondents at the level of recruitment, the screening questionnaire includes five items dealing with respondents’ motivation to try a web-based interventions. Three items assess respondents’ anticipated usefulness of a web-based intervention, one item assesses their willingness to try a web-based intervention, and one item assesses respondents’ computer skills with regards to the application of a web-based intervention. All items are rated on a 4-point Likert scale.

#### Sample characteristics

##### Demographic variables

Socio-demographic variables are assessed at baseline, based on the recommendations of Deck and Röckelein [68]. These variables include age, gender, family status, education, employment, diseases, and former psychotherapy.

##### Internet affinity

Internet affinity is measured using the Internet Affinity Scale (IAS; [69]). The IAS measures internet affinity and frequency of internet usage with six items to be rated on a 5-point Likert scale. The scale’s reliability is good (*α* = .84; [69]). One additional item assesses computer-related competencies and will be evaluated separately.

##### Health care utilization

For the assessment of utilized health care services, the Questionnaire for Health-Related Resource Use in an Elderly Population (FIMA; [70]) is applied in an adapted version; items dealing with seniority-specific aspects, such as the usage of nursing services or domestic help, are left out. The remaining ten items assess the number of utilized health care services of the past eight weeks, as well as the current intake of medication. One additional item assesses the use of additional psychological health care options, such as bibliotherapy and self-help groups.

##### Current Psychotherapy

At all points of assessment participants indicate their current motivation and their perceived need for psychotherapy, and whether they are currently receiving face-to-face psychotherapy. Participants indicating their current receipt of psychotherapy are asked how many sessions they have had and when their first appointment has been. Participants not receiving face-to-face psychotherapy are asked to indicate reasons.

## Statistical analyses

### Effectiveness analyses

Analyses will be based on an intention-to-treat principle by including all randomized participants into the analyses. Primary and secondary outcomes will be analysed using a linear mixed model, assuming data are missing at random. The mixed model for the primary outcome (depression) will include group, time (all three points of assessment) and the interaction of group and time as fixed effects and recruiting outpatient clinic as random effect. Secondary outcomes will be analysed accordingly. We will calculate between-group effect sizes for the primary outcome using the post-treatment depression means and their pooled observed standard deviation. Additional per protocol analyses will include only those participants who have not started psychotherapy until the end of all study procedures, completing all three assessments, and, regarding the intervention group, at least five intervention modules.

We will evaluate the clinical relevance of any given development in a generalized linear model by estimating numbers of treatment response and deterioration (based on the reliable change index; [71]) and symptom remission (ADS-L score < 22; [41]), and by calculating the number needed to treat (NNT) for one more remitted participant.

Potential moderators influencing treatment effects will be analysed in the mixed model analysis. As there is at this point little research concerning moderating variables in the field [72], these analyses follow an exploratory approach. Potential influencing variables include socio-demographics, internet affinity or attitudes towards psychotherapy.

Analyses will be performed using an alpha level of .05 and two-sided tests. All analyses will be conducted using IBM SPSS.

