### Recruitment

Participants are recruited at several psychotherapeutic outpatient clinics in Germany. All cooperating outpatient clinics have a current wait of at least two months before individuals enter psychotherapy. Consecutively, all those accepted onto the waitlist of an outpatient clinic are informed about the ongoing study and receive study information and screening material. All individuals on the existing waitlists with a remaining waiting time of at least two months are also invited to fill in screening material. Screeners are sent back directly to the research team. Respondents are tested for eligibility to participate in the study (cf. inclusion criteria). Eligible respondents receive an e-mail providing further study information and a link to the digital informed consent sheet. All respondents giving their informed consent are enrolled in the online baseline assessment (T1) and then randomized either to the intervention group (IG) or the control group (CG). Participants of the IG are provided with a link to access the web-based intervention. Participants of the CG are given the opportunity to access the web-based intervention without guidance after follow-up assessment. Recruitment has started in February 2017 and is ongoing until both treatment arms have reached a size of *n* = 68. All procedures were specified prior to recruitment start and are conducted as explicated in the clinical registration form (DRKS00010282).

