### Inclusion and exclusion criteria

Individuals waiting for psychotherapy in one of the cooperating outpatient clinics and interested in study participation are eligible when they indicate (1) an age of 18 years and over, (2) working internet access, and (3) depressive symptoms (CES-D score > 22; Center for Epidemiologic Studies Depression Scale [42]). Exclusion criteria are reduced to a minimum. This procedure allows for high external validity as it leads to a heterogeneous sample of people seeking outpatient psychotherapy independent of a particular diagnosis. It allows individuals with other primary diagnoses (e.g. anxiety disorder) to participate in the study, as long as they show substantial depressive symptoms. Comorbid psychological symptoms are detected with the Brief Symptom Inventory (BSI; [43]). As additional criterion, participants must (4) submit their informed consent, (5) complete baseline assessments and (6) state no suicidal ideation on the BSI item no. 9 (score < 2). In case of a BSI item score of 1, participants must agree to a non-suicide-contract before entering the study. In case of suicidal ideation throughout the study, we follow a firm suicide protocol, which has been approved by the ethics committee. Potential steps in case of suicidal ideation include information on further help, non-suicide contracts, and telephone calls by a licensed psychotherapist.

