### Proposed sample size

The sample size calculation is based on the difference in change in the primary outcome (depressive symptoms) from pre- to post-treatment in both treatment arms (intention-to-treat analysis). Considering recent meta-analytic effect sizes for web-based depression interventions, an effect size of *d* = 0.56 [33] can be expected and is considered feasible for the type of intervention (guided intervention, naturalistic study design, cf. [44]). On the basis of a two-sample t-test at a two-sided significance level of .05, the study is planned to detect this effect with 90% power. This requires a sample of 68 individuals in each arm.

With a target sample size of *N* = 136 for randomization, at least 597 screeners have to be sent out. Based on previous research, it is expected that about 50% of the contacted people are interested in study participation [37]. Further, about 65% of those interested are expected to score above the cut-off for depressive symptoms [45], resulting in 194 potential participants. A 30% loss is expected due to incomplete baseline, suicidal ideation or missing informed consent, leaving 136 participants for randomization.

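### The primary mixed model lets the arms differ freely at the pre-randomisation baseline instead of adjusting for it; the analysis is valid but gives up precision that could be had at no data cost

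*Protocol article*

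**What the plan says.** Effectiveness analyses specifies the primary model: "The mixed model for the primary outcome (depression) will include group, time (all three points of assessment"). The other terms named are a group-by-time interaction and a random clinic effect. T1 is therefore part of the outcome vector, and the group term allows a separate T1 mean in each arm. No baseline covariate and no equal-baseline constraint is stated anywhere. Moderators are a separate exploratory analysis. Secondary outcomes follow the same model. The effect size to be reported comes from raw post-treatment means and their pooled SD, so it is unadjusted too.

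Under Recruitment, participants are "enrolled in the online baseline assessment (T1) and then randomized". Under Inclusion and exclusion criteria, participants must "complete baseline assessments". T1 therefore precedes allocation and exists for everyone randomised.

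Proposed sample size states: "The sample size calculation is based on the difference in change in the primary outcome (depressive symptoms) from pre- to post-treatment". It then takes d = 0.56 and an unadjusted t-test at a two-sided 5% level, and says that "the study is planned to detect this effect with 90% power". The result is 68 per arm.

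**The concern.** Because T1 is taken before randomisation, any T1 difference between the arms is chance. A model with a free group effect at T1 estimates that difference and subtracts it in full from the T2 difference. With complete data this is a change-score comparison. It removes more of the baseline than the T1–T2 relation warrants whenever the regression of T2 on T1 has a slope below 1, and the excess is noise.

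What is at stake is the width of the confidence interval and the power of the main comparison, and likewise for each secondary outcome with a T1 value. The data for a sharper estimate are already collected.

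**Working it through.** **Inputs from the protocol article.** d = 0.56, two-sided alpha 0.05, 90% power, 68 per arm, 1:1 allocation, T1 before randomisation and complete.

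**Assumptions, not in the article.** Correlation rho between T1 and T2 CES-D (0.3 to 0.7); ratio k = SD(T2)/SD(T1); a participant-level covariance; the T2 group-by-time contrast as the primary one, in line with the sizing statement. The article does not say whether d is standardised on the T2 SD or the change-score SD, so both are shown.

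**Step 1, the plan's own figure.** A two-sample t-test at d = 0.56 needs 68 per arm; exact power at 68 is 0.900. The stated number reproduces.

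**Step 2, variances with complete data and equal SDs (k = 1).** Each is multiplied by 2·SD²/n.
- Planned group-by-time contrast at T2: 2(1 − rho)
- Adjusted for T1, or common T1 mean: 1 − rho²
- Ratio, adjusted to planned: (1 − rho²)/[2(1 − rho)] = (1 + rho)/2

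| rho | Planned | Adjusted | Ratio | Planned SE larger by |
|---|---|---|---|---|
| 0.3 | 1.40 | 0.91 | 0.65 | 24% |
| 0.5 | 1.00 | 0.75 | 0.75 | 15% |
| 0.7 | 0.60 | 0.51 | 0.85 | 8.5% |

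Generalised least squares with three occasions and compound symmetry gives the same ratios. If the plain T2 group difference from the planned model were tested instead, the ratio would be 1 − rho²: 0.91, 0.75 and 0.51. Neither contrast matches adjustment for rho strictly between 0 and 1.

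**Step 3, unequal SDs.** The ratio becomes k²(1 − rho²)/(k² + 1 − 2k·rho). At rho 0.5:
- k = 1.2: 1.08/1.24 = 0.87
- k = 1.3: 1.2675/1.39 = 0.91
- k = 1.5: 1.6875/1.75 = 0.96

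Entry requires a screening CES-D above 22, which can narrow the T1 spread while T2 is free to widen, so k above 1 is plausible.

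**Step 4, power at 68 per arm, complete data, k = 1.**

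| rho | d on T2 SD: planned | d on T2 SD: adjusted | d on change SD: planned | d on change SD: adjusted |
|---|---|---|---|---|
| 0.3 | 0.78 | 0.925 | 0.90 | 0.980 |
| 0.5 | 0.90 | 0.963 | 0.90 | 0.963 |
| 0.7 | 0.987 | 0.995 | 0.90 | 0.940 |

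**Step 5, missing T2.** Let a share p be observed after T1, with those lacking T2 also lacking T3. The planned mixed model still uses the T1 values of people who drop out. The planned variance is (1 − rho²)/p + (1 − rho)², and the adjusted variance is (1 − rho²)/p. At rho 0.5, k = 1 and d on the T2 SD:
- p = 0.8: planned 0.9375 + 0.25 = 1.1875, adjusted 0.9375, ratio 0.79; power about 84% against 92%
- p = 0.7: planned 1.0714 + 0.25 = 1.3214, adjusted 1.0714, ratio 0.81; power about 80% against 88%

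**The case against.** The planned model is standard and unbiased under randomisation, and it fits the sizing statement, which is about the difference in change. If d = 0.56 is read on the change scale, as that statement suggests, the trial keeps its 90% with complete data and adjustment only adds to it. All of this stands, and it makes the point one of efficiency.

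Four stronger readings are tempting and are not supported:
- **That the result would be biased or the sample size wrong.** Neither follows: the contrast is valid and 68 per arm reproduces.
- **That the baseline is thrown away.** The change contrast uses it; only part of its information is lost.
- **That dropout takes the planned power to 82.5% (20% missing) or 77% (30% missing) at rho 0.5.** Those figures describe a completers-only change score. The article plans a mixed model under missing at random on all randomised participants, which gives about 84% and 80%.
- **That (1 + rho)/2 is a known gain.** It needs equal SDs and a value of rho, and the article gives neither. At rho 0.5 and k = 1.3 the variance saving is about 9%, not 25%.

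Whether the sample size should allow for dropout is a separate question and adds no weight here.

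**Conclusion.** The point holds as a loss of precision, not as an error. The model as written is less efficient than one that adjusts for T1 or shares a T1 mean. With equal SDs, complete data and a participant-level covariance, adjustment cuts the variance of the T2 contrast by 35%, 25% or 15% at rho 0.3, 0.5 or 0.7. A larger SD at T2 reduces the saving, and missing T2 data reduce it somewhat too. In power terms, at rho 0.5 with equal SDs and d on the T2 SD, adjustment adds about 6 points with complete data and about 8 points with 20% or 30% missing T2. The direction rests on the design alone; the size rests on rho, k and the scale of d, which the article does not give. It is worth changing because the value is already collected for everyone.

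**What to change.** Before the treatment variable is added to the data set, specify one of two models:
- Keep T1, T2 and T3 as outcomes, with fixed effects for time and group by post-baseline time, no group effect at T1, and a participant-level covariance.
- Model T2 and T3 as outcomes, with T1 CES-D and T1 CES-D by time as covariates.

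Report the adjusted T2 difference with its 95% CI, and do the same for each secondary outcome measured at T1. The cost is one sentence in the analysis plan and a change to the prepared syntax. No extra data and no change to the sample size are needed.

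### E-coaches act in the intervention arm only, but clinic is the only random effect named; add a prespecified partially nested sensitivity analysis

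*Protocol article*

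**What the plan says.** Under Intervention condition, the protocol article describes the guidance: "Participants receive a semi-standardized feedback after each completed module by an e-coach (trained psychologist) in order to enhance adherence". On its content it adds: "Feedback includes positive reinforcement of the participants’ assignments and encouragement to continue working with the intervention". The coaches appear in the plural: "E-coaches are not otherwise involved in the study". Their number, their caseloads and how participants are assigned to them are not given.

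Controls have no coach before follow-up. Under Recruitment: "Participants of the CG are given the opportunity to access the web-based intervention without guidance after follow-up assessment".

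Under Effectiveness analyses, the primary model contains group, time, "the interaction of group and time as fixed effects and recruiting outpatient clinic as random effect". No other random effect is named. For the other outcomes: "Secondary outcomes will be analysed accordingly".

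Under Proposed sample size, the effect of d = 0.56 "can be expected and is considered feasible for the type of intervention (guided intervention, naturalistic study design". The calculation treats participants as independent: "On the basis of a two-sample t-test at a two-sided significance level of .05, the study is planned to detect this effect with 90% power". The result is 68 per arm.

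**The concern.** This is a partially nested design: intervention participants may be clustered by coach, while each control stands alone. The article treats guidance as part of what is tested and cites it to support the assumed effect size. It also says the feedback is only partly standardised. Outcomes may therefore differ by coach.

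The article does allow for one source of clustering, the recruiting clinic. Both arms share that source, so a clinic effect largely cancels from the treatment comparison. Coach variation does not cancel, because it enters one arm mean only. If it is present and left out, the standard error of the treatment contrast is too small, the test rejects too often, and the planned power is optimistic. The same holds for the secondary outcomes, which follow the same model.

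**Working it through.** **Inputs from the article (Proposed sample size):** d = 0.56 (SD 1), two-sided alpha 0.05, power 90%, 68 per arm.

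**Assumptions, not in the article:** k coaches with equal caseloads m = 68/k; coach ICC; each intervention participant keeps one coach; all 68 receive feedback.

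**1. The plan's own figure.** The exact noncentral t calculation gives power 0.9001 at 68 per arm and 0.8957 at 67. The stated 68 reproduces, with no allowance for coach clustering.

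**2. Coach clustering in one arm, post-treatment difference.**

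- Design effect in the intervention arm: DE = 1 + (m − 1) × ICC
- True SE / model SE: r = √((1 + DE)/2)
- Actual type I error: 2 × (1 − Φ(1.96/r))
- Power with the correct SE, normal approximation: Φ(0.56/√((1 + DE)/68) − 1.96)

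Example with k = 4 and ICC 0.02: m = 17; DE = 1 + 16 × 0.02 = 1.32; r = √1.16 = 1.077; type I error = 2 × (1 − Φ(1.820)) = 6.9%; power = Φ(0.56/√(2.32/68) − 1.96) = 86%.

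| Coaches | ICC | DE | r | Type I error | Power, correct SE |
|---|---|---|---|---|---|
| any | 0 | 1.00 | 1.00 | 5.0% | 90% |
| 4 | 0.01 | 1.16 | 1.04 | 5.9% | 88% |
| 4 | 0.02 | 1.32 | 1.08 | 6.9% | 86% |
| 4 | 0.05 | 1.80 | 1.18 | 9.8% | 79% |
| 8 | 0.01 | 1.08 | 1.02 | 5.4% | 89% |
| 8 | 0.02 | 1.15 | 1.04 | 5.9% | 88% |
| 8 | 0.05 | 1.38 | 1.09 | 7.2% | 85% |

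Simulation of a t-test that ignores coach (20,000 runs each) agrees: 6.9% and 9.9% for 4 coaches at ICC 0.02 and 0.05, and 5.9% and 7.4% for 8 coaches.

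**3. Partial exposure.** Feedback follows a completed module, so a participant who completes none receives none but stays in the intention-to-treat set. As an illustration, suppose 34 of the 68 are coached by 4 coaches (m = 8.5). The variance of the intervention mean is then (DE + 1)/136. At ICC 0.02, DE = 1.15 and the type I error is 5.4%, against 6.9% with full exposure. At ICC 0.05, DE = 1.375 and it is 6.1%, against 9.8%.

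**4. Repeated measures.** For the baseline-to-post change contrast, take unit variance, within-person correlation 0.5, 4 coaches and ICC 0.05. In units of 1/68, the true variance is 4 × (1 − 0.5) + 16 × 0.05 = 2.8.

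- With participant correlation modelled and coach omitted, the model uses 2.0: SE ratio √(2.8/2.0) = 1.18.
- With clinic as literally the only random effect and residuals taken as independent, it uses 4.0: SE ratio √(2.8/4.0) = 0.84, so the SE is too large.

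**5. Cost of a coach term in the primary model.** With small-sample degrees of freedom (Satterthwaite: k − 1 for the intervention mean, 67 for the control mean), 4 coaches give df of about 11.5 and power of about 85% at ICC 0, and df of about 9 and power of about 77% at ICC 0.02. Two coaches at ICC 0.02 give df of about 2.5 and power of about 44%.

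**The case against.** The strongest objection is that the nesting is inferred. The article does not say that a participant keeps the same coach, and shared caseloads would dilute the clustering. The feedback is partly standardised and consists of reinforcement and encouragement, while the therapeutic content sits in the programme, so the ICC may be close to zero. This stands, and it is why the size is left open.

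Second, a reader might infer that any between-coach variation makes the reported SE too small. The article does not support that. Step 4 shows that the literal model, with no participant-level term, can overstate the SE of the change contrast by more than coach effects understate it. The direction holds only once within-participant correlation is modelled.

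Third, randomisation is individual. If the intervention affects nobody, whichever coach delivers the feedback, this source adds no variation and no inflation. The inflated error rate applies to inference about coaches in general, where effects differ between coaches but average to zero. The article does not say which inference it intends. This also stands.

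Fourth, a reader might conclude that the primary model must contain a coach effect. Step 5 shows that with few coaches this can cost more power than the problem warrants, even when the ICC is zero.

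Finally, the article is condensed, and a fuller plan might deal with coaches. That is a fair reason for a modest recommendation. It does not remove the point, because the article states the random-effect structure and names a single source of clustering, which is not the one confined to one arm.

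**Conclusion.** The point holds in a conditional form. The one-arm coach structure is documented, and the named random effect cannot represent it. The treatment SE is understated if three things hold together: coach effects exist, participants mostly stay with one coach, and within-participant correlation is modelled. Even then the understatement concerns inference beyond the coaches in this trial.

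Under the assumed 4 to 8 coaches and ICC 0.01 to 0.05 with full exposure, the SE is 2% to 18% too small relative to the model's own value (r = 1.02 to 1.18), and type I error is 5.4% to 9.8%. Since 68 per arm only just reaches 90%, power with the correct SE falls to between 89% and 79%. Partial exposure shrinks these figures, and an ICC of zero removes them. The article does not allow a narrower range. This is a worthwhile, inexpensive safeguard and not evidence that the primary analysis is invalid.

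**What to change.** Record the e-coach for each intervention participant, including any change of coach. Keep the stated primary model. Prespecify one sensitivity analysis that adds an e-coach random effect in the intervention arm only, with controls as singletons and small-sample degrees of freedom, and report the estimated coach variance next to the primary result. If there are too few coaches to estimate that variance, show the treatment interval over a range of assumed ICCs, starting at zero.

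The cost is one stored identifier and one extra analysis, with an imprecise variance estimate and a wider interval. Recruitment and treatment are unchanged. The identifier should be stored while the trial runs, because it may be hard to reconstruct afterwards.
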